### Results of Project's Implementation

To answer the research questions regarding the effectiveness of the projects, we utilize the RE-AIM framework and its five dimensions: “reach,” “efficacy,” “adoption,” “implementation,” and “maintenance” (32). Using the RE-AIM framework allows us to address our research questions in regard to the ability of communities to generate public health impact by implementing the two exercise interventions which are targeted at vulnerable groups. Additionally, as mentioned by Kwan et al. (33) it “provides structure to systematically evaluate health program impact.”

We will conduct annual semi-structured interviews with the project's coordinators of the 15 communities (*n* = 45 interviews), as well as annual semi-structured focus groups with peers (*n* = 30 interviews) in each setting. Additionally, quantitative data will be collected, including an annual evaluation of capacity building using a standardized questionnaire filled out by the projects' coordinators, all attendance lists of the BIG-5 and GET-10 exercise courses, including number of people on the waiting lists, and data on satisfaction using a standardized short feedback questionnaire filled out by the course participants. Table 3 describes all study evaluation methods, participants, and study parameters.

**Table 3 T3:** Evaluation methods.

		**Participants**	**Time of measurement**	**Topics of interest**	**Total**	**RE-AIM indicator**
Recruiting communities for scale-up	Semi-structured telephone interviews	All interested communities		- Who contacted the researcher? - How did they receive information? - Is there a specific reason why they want to implement the project? - Do they have previous or similar health promotion projects?		-
	Timeline documentation	All interested communities	From first contact until decision making or project implementation	- How long do communities take until making a decision? - Do we reach communities that are the most in need?		-
	Web-based search	Participating communities + interested communities + 10 most deprived Bavarian communities		- How active are communities regarding health promotion? - Do we reach communities that are the most in need? - Percentage of the target population in the community		-
Results of projects' implementation	Semi-structured interviews	Community coordinators (*n* = 15)	Annually	- Barriers and facilitators in reaching the target population - Adaptations made to the cooperative planning method - Capacity-building areas: (1) participation, (2) local leadership, (3) available resources, (4) networking and cooperation, (5) health care - Efforts made for the durable implementation	*n* = 45	Effectiveness, adoption, implementation, maintenance
	Semi-structured focus group	Peers (*n* = 15)	Annually starting from year 2	- Barriers and facilitators during work as peers - Satisfaction with the courses - Empowerment of peers Capacity-building areas: (1) participation, (2) local leadership, (3) available resources, (4) networking and cooperation, and (5) health care	*n* = 30	Effectiveness, adoption, implementation
	Attendance lists		Every course	- Reach of target population		Reach, effectiveness
	Waiting lists		Every course	- Reach of target population		Reach, effectiveness
	Satisfaction questionnaire	Participants of courses	After each course	- Satisfaction with the course incl. time, length, difficulty, trainer, and instructions		Effectiveness
	Capacity-building questionnaire	Community coordinators (*n* = 15)	Annually	-Capacity-building areas: (1) participation, (2) local leadership, (3) available resources, (4) networking and cooperation, (5) health care	*n* = 45	Adoption, implementation, maintenance

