## Methods and Analysis

The projects receive funding from the Federal Centre for Health Education. Communities located in Bavaria, Germany, with over 5,000 inhabitants can apply for funding for one of the projects by contacting the scientific coordinators. Using a low-threshold application scheme, communities have to send an expression of interest signed by the local major to the funding agency. Based on the expression of interest and some other formal criteria, communities receive funding.

During the project work, the 15 communities function as so-called “real-world laboratories” that “contribute to capacity development, new scientific insights and societal learning, building on iterations of experimentation and reflection” (25). In this process, real-world laboratories aim at meeting four characteristics: (1) follow transformative science approaches (e.g., testing out solutions to reduce health inequalities), (2) establish the mechanisms of coproduction between science and health promotion practice, (3) follow transdisciplinary approaches (i.e., scientific, policy, and practice) and to enable the target population to work together in finding possibilities of intervention implementation and sustainability of the project, and (4) plan for a durable scaling-up of implementation (26).

Communities will implement a predeveloped project plan for one of the two projects, as visualized in Tables 1, 2. During implementation, they will receive guidance and scientific support. Both projects are similar as both target disadvantaged population groups and adopt a participatory approach that enables communities to establish and sustain target group-specific interventions for PA. Using the participatory method of cooperative planning (23, 24), the projects aim to include members of the target group, researchers, community administrative staff, and practitioners (e.g., staff from local sport clubs or other health departments) in the planning and implementation of interventions for promoting PA among the target group. Coordinators will receive a manual on how to conduct the cooperative planning method (27), including a detailed description of all the steps. Based on the participatory nature of the projects, some actions taken may vary between the communities.

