### Recruiting Communities for Scale-Up

To evaluate the recruitment process of the communities, all contact between the researchers and the interested community members will be systematically documented. Interested community members will engage in one-on-one phone calls with researchers. During the call, the researchers will ask standardized questions to gather information on (a) how the communities learned about the projects (e.g., via newsletters, social media posts, or through colleagues), (b) who contacted the researchers (e.g., mayor, health department, external partner, etc.), (c) why they were interested in the project, and d) if they had previous experience or carried out similar projects in the past.

Additionally, data will be collected on all the interactions with the communities until they have made a final decision to take part. This will include (a) the time it took, (b) the number of contacts, and (c) the factors that the communities mentioned as influencing their decision.

A systematic web and database search and qualitative content analysis, here according to McMillan et al. (29), will complement the systematic documentation by identifying each community's (1) population size, (2) community deprivation index developed by Kroll (30), (3) previously implemented health promotion programs, and (4) the percentage of target population among inhabitants and other potentially relevant factors (e.g., party alignment in city councils). To generate additional data on the communities most in need, the community deprivation index will be utilized (30).

The collected data will be analyzed using qualitative content analysis (31) to make comparisons among the following three groups: (a) participating communities, (b) interested communities that did not apply for funding, and (c) communities most in need according to the community deprivation index that match the funding criteria (located in Bavaria with inhabitants totaling over 5,000).

The analysis will identify the time period needed by communities to reach a decision, barriers and facilitators that led to the decision, number of already existing health-promotion projects in the communities, and whether socioeconomically deprived communities are being reached by the funding scheme.

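### Whether deprived communities are reached is judged against self-selected non-applicants and the ten most deprived communities, never against all eligible communities, so the answer will be weak and easily misread

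*Protocol article*

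**What the plan says.** In the Protocol article, Recruiting Communities for Scale-Up (under Methods and Analysis), one stated purpose of the recruitment analysis is to find out "whether socioeconomically deprived communities are being reached by the funding scheme". The method is given as follows: "The collected data will be analyzed using qualitative content analysis (31) to make comparisons among the following three groups". Participants form group (a). Those that showed interest without going on to an application form group (b). For group (c) the definition reads "communities most in need according to the community deprivation index that match the funding criteria (located in Bavaria with inhabitants totaling over 5,000". No number is set for group (c). The deprivation index is recorded for each community in the web and database search.

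Table 3, web-based search row, lists the communities searched as "Participating communities + interested communities + 10 most deprived Bavarian communities". It gives the number ten and does not repeat the size limit. One topic of that row, shared with the timeline row above it, is "Do we reach communities that are the most in need". Eligibility is set at the start of Methods and Analysis: "Communities located in Bavaria, Germany, with over 5,000 inhabitants can apply for funding for one of the projects".

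The Adoption section compares communities that take part with those that do not, using information gathered during recruitment, and therefore only communities that made contact. Aims and Objectives gives the number of participants as five plus ten, that is 15.

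**The concern.** Whether a scheme reaches deprived communities is a question about where its participants fall among the communities that could have joined. That needs the index distribution of the eligible communities, and the article plans no comparison with it. Interested non-applicants chose to make contact, so they do not represent the eligible communities. The ten most deprived are the extreme tail, so they show what the far end looks like but not where the middle lies.

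A scheme that recruits mostly from the deprived end could therefore be reported as missing the communities most in need, simply because its participants are less deprived than the ten or because few of the ten joined. The Abstract and its Conclusion present reaching the settings most in need as a main product of the study, so a misread answer would matter.

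A smaller point is that the text and Table 3 describe the most-deprived group differently. Read literally, Table 3 could admit communities too small to apply, whose absence would say nothing about reach.

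**Working it through.** The article gives no figure for this comparison, so there is nothing to reproduce. The check asks what the planned contrast could show.

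**Inputs.** Participants: 15 (Aims and Objectives). Most-deprived group: 10 (Table 3). Number of eligible communities, N: not in the document; assumed 200 to 800.

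**1. Comparing index values.** Let a higher index mean more deprived, and let m be the mean of the ten most deprived. Fifteen participants include at least 15 − 10 = 5 from outside the ten. Each of those has an index below the tenth-ranked community, hence below m. The highest mean that 15 participants can reach is that of the 15 most deprived communities, (10m + the sum of ranks 11 to 15)/15, which is less than m when there are no ties. A simulation with a standard normal index (2,000 replicates) agrees:

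| N | Ten most deprived | 15 most deprived | 15 from most deprived fifth | 15 at random |
|---|---|---|---|---|
| 200 | 2.04 | 1.87 | 1.40 | 0.0 |
| 400 | 2.32 | 2.17 | 1.40 | 0.0 |
| 600 | 2.47 | 2.32 | 1.40 | 0.0 |

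(Mean index in SD units; eligible mean 0.) Random recruitment and recruitment wholly from the most deprived fifth both fall below the ten in 100% of replicates. Against the mean of all eligible communities they separate: about 0 versus about +1.4 SD.

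**2. Counting participants among the ten.** If recruitment is unrelated to deprivation, the expected overlap is 15 × 10/N = 150/N, and the chance of no overlap is C(N−10, 15)/C(N, 15). If all 15 come from the most deprived fifth, N/5 replaces N.

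| N (assumed) | Expected, neutral | Chance of none, neutral | Expected, most deprived fifth | Chance of none, most deprived fifth |
|---|---|---|---|---|
| 200 | 0.75 | 45% | 3.75 | 0.4% |
| 300 | 0.50 | 59% | 2.50 | 4% |
| 400 | 0.38 | 68% | 1.88 | 11% |
| 600 | 0.25 | 77% | 1.25 | 25% |
| 800 | 0.19 | 83% | 0.94 | 36% |

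At N = 400 the chance of two or more overlaps is 5% under neutral recruitment and 60% from the most deprived fifth. The count does discriminate, clearly for a short eligible list and weakly for a long one. With a long list, no overlap is likely under neutral recruitment and still quite possible under strong targeting.

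**3. Precision of the proposed alternative.** Neutral recruitment puts 15 × 0.20 = 3 communities in the most deprived fifth. Exact (Clopper–Pearson) 95% intervals are 4% to 48% for 3 of 15, 16% to 68% for 6 of 15, and 21% to 73% for 7 of 15. About 7 of 15 would be needed before the interval excludes 20%.

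**The case against.** The best case for the plan is that it never states a comparison of mean index values. In the text the index serves to pick out the communities most in need. The first topic of the web-search row is how active communities are in health promotion, and for that a small set of extreme cases is ordinary qualitative sampling. Interested non-applicants are compared too, and the timeline row addresses need among all interested communities. The comparison has no test, threshold or decision rule. The proposed share would also be imprecise and comes from self-selected applicants.

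Most of this stands, and it limits the point. A reader might infer that the ten are the sole benchmark, that participants will look less deprived by construction, or that the plan cannot tell neutral from favourable recruitment. The article supports none of these. Group (b) is a second comparator. The ordering result applies only if mean index values are set against the ten; it would not be strict if the ten were limited to non-participants, which the article does not say. The overlap count carries some information at every N in the table.

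A reader might also infer that Table 3 withdraws the size limit. More probably the cell is shorthand and the explicit criterion in the text governs. Whether the index behaves differently for municipalities and rural districts depends on how it is built, which is not shown, so nothing is claimed on that. Naming content analysis for the three-group comparison is not a fault in itself, since a condensed article may leave numerical summaries to a fuller plan.

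What the objection leaves untouched is that the article asks whether deprived communities are reached, and none of its stated comparators shows where participants stand among the communities that could have applied.

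**Conclusion.** The point holds as a gap in the reference group. The two comparators are a self-selected group and an extreme tail, so the answer on reach will be weak and open to misreading. If index means are compared with the ten, participants will appear less deprived however well the scheme targets. If overlap is counted, finding none has probability 45% to 83% under neutral recruitment and 0.4% to 36% under recruitment wholly from the most deprived fifth. These ranges rest on an assumed 200 to 800 eligible communities, on the ten being drawn from the eligible list without excluding participants, and on random draws within each scenario.

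The consequence is a misleading description, not an inflated error rate. This should be fixed, but it is not critical. The difference in wording between Table 3 and the text is a minor matter to reconcile.

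**What to change.** Add one descriptive comparison. List all Bavarian communities with over 5,000 inhabitants, and give each participating and each interested community its percentile or fifth of the deprivation index within that list. Report the share of participants in the most deprived fifth against the 20% expected under neutral recruitment, with an exact 95% confidence interval, and say in advance that it will be wide with 15 communities.

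Keep the web search of the ten as a qualitative comparison of health-promotion activity. Reconcile Table 3 with the text by limiting the ten to communities that match the funding criteria, and say whether a participating community may be one of them.

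The cost is a little more analysis with an index the plan already uses and no new fieldwork, provided index values can be obtained for all eligible communities. The downside is an imprecise estimate, but one that addresses the question the article asks.

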#### Reach

During the annual interviews, coordinators will be asked about the efforts made to reach the specific target group, as well as the barriers and facilitators in reaching participants. Because peers of the target group act as social catalysts in recruiting participants and in advertising, they will be asked to report on their experiences, including the barriers and facilitators in reaching the target population. Additionally, attendance lists of exercise courses in each community will be gathered, including the number of participants on potential waiting lists. These data will be used to analyze how offers reach the target group. We will look specifically at the differences in reach between GET-10 and BIG-5.

#### Efficacy

Efficacy will be assessed in the GET-10 project by questionnaire to assess the PA levels of the participants in the classes. Efficacy in the BIG-5 project will be assessed by the attendance lists by looking into the demographics of course participants and compare them to overall demographics of the community.

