## Conclusion

Scale-up and sustainment of community-based participatory research projects is crucial to reduce health inequalities. The two interventions have already been evaluated and demonstrated effectiveness. The current study can provide additional evidence on the barriers and facilitators of scale-up and sustainability, capacity building within a community setting through health promotion projects, and the project's effects on the target populations. Through a cross-sectional examination of the recruitment process of communities, the current study will be the first to provide evidence on how to reach communities to engage in such projects and the barriers and facilitators for implementation they may face.

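### BIG-5 efficacy is defined by a demographic comparison that measures reach, and the GET-10 physical activity questionnaire is missing from the table said to hold all evaluation methods

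*Protocol article*

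**What the plan says.** The section Results of Project's Implementation uses RE-AIM to answer questions about how effective the projects are. Its Efficacy subsection treats the two projects differently.

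- **GET-10:** "Efficacy will be assessed in the GET-10 project by questionnaire to assess the PA levels of the participants in the classes". No instrument, time point or comparison follows.
- **BIG-5:** "Efficacy in the BIG-5 project will be assessed by the attendance lists by looking into the demographics of course participants"; the plan is then to "compare them to overall demographics of the community".

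The Reach subsection draws on the same attendance lists, together with waiting lists, and says: "These data will be used to analyze how offers reach the target group". In Table 3 the only topic for both kinds of list is "Reach of target population", yet the RE-AIM column tags both rows as reach and effectiveness.

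On completeness, the text states: "Table 3 describes all study evaluation methods, participants, and study parameters". The one questionnaire for course participants in that table is given after each course and covers "Satisfaction with the course incl. time, length, difficulty, trainer, and instructions".

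The Conclusion lists "the project's effects on the target populations" among the evidence that the study can provide.

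**The concern.** A measure labelled efficacy should be able to move when the intervention works and stay still when it does not. The BIG-5 measure cannot do this. Attendees' background characteristics are settled before the first class, so the comparison with the community would look the same whether or not any class changed anyone's activity.

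The GET-10 measure is of the right kind, but it stands in one sentence only. A questionnaire that is absent from the evaluation schedule may be given inconsistently, or not at all, across ten communities run by local coordinators.

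The Introduction warns that effects may shrink when interventions are scaled up and calls maintaining efficacy a relevant research topic. If the plan is followed as described, BIG-5 would report a reach result under an efficacy heading. GET-10 might have no PA data to report. Pre-course values cannot be recovered once a course has started.

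**Working it through.** The document gives no sample size, power or effect size for efficacy, so there is no figure to reproduce. The check sets the relevant places side by side.

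**1. What the BIG-5 measure can show**

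| Place | Data source | Stated use |
|---|---|---|
| Efficacy | Attendance lists | Attendees' demographics against the community's |
| Reach | Attendance and waiting lists | How far the target group is reached |
| Table 3, topic column | Attendance and waiting lists | Reach only |
| Table 3, RE-AIM column | Attendance and waiting lists | Reach and effectiveness |

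Two of the four entries treat the lists purely as reach data. The other two call them efficacy or effectiveness data without adding a variable that could reflect an effect. No PA or health outcome in BIG-5 course participants is described anywhere.

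**2. Whether the GET-10 questionnaire is scheduled**

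- Table 3 has 3 recruitment rows and 6 implementation rows, 3 + 6 = 9 in all.
- Two rows are questionnaires: satisfaction (participants, after each course) and capacity building (coordinators, annually). Neither covers participants' PA.
- The list of quantitative data in the text before Table 3 names the capacity questionnaire, attendance lists with waiting-list numbers, and the satisfaction form. It names no PA questionnaire.
- The Abstract mentions a standardized questionnaire for course participants without saying what it covers, so it does not settle the matter.

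Rows of Table 3 that measure participants' PA: 0 of 9.

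**3. What stands behind the effectiveness tags**

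Five rows carry the tag: coordinator interviews, peer focus groups, attendance lists, waiting lists and the satisfaction questionnaire. Rows among these with a PA or health outcome in participants: 0 of 5.

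**4. Extent**

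- BIG-5: 5 communities × 18 classes = 90 planned classes, with satisfaction and attendance recorded but no PA or health outcome described.
- GET-10: 10 communities × 4 cycles = 40 course cycles, for which a PA questionnaire is named in the text but not scheduled.

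**The case against.** The best defence is that this is a scale-up evaluation and not an effect study. The key questions under Aims and Objectives concern recruitment, capacity, barriers and facilitators, and reaching the target population; none asks about individual PA change. The limitations concede that no randomized design is in place and that information on effectiveness will be limited. The section on Implementation and Maintenance also says that those two dimensions can count as effectiveness of the implementation strategies, which partly explains the broad tags in Table 3. This stands as far as severity goes. It does not cure the mismatch: the concession is about design and does not say that BIG-5 measures no PA, and the Conclusion still offers evidence on effects.

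Several stronger readings are tempting, and the documents do not support them.

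- *GET-10 has no baseline, or measures PA only once.* The text is silent on timing. The after-course timing in Table 3 belongs to the satisfaction form. A full protocol could contain a pre-course measurement, and an article may leave such detail to it.
- *BIG-5 measures no outcome at all.* Satisfaction is collected after each course, and peer focus groups explore empowerment.
- *The plan fails to reproduce an earlier result or to compare efficacy between projects.* The Introduction reports that 60% of GESTALT participants increased PA outside class, but as background and not as a benchmark. The promised comparisons between projects concern reach, capacity, and efforts to implement and maintain.
- *The overall community is plainly the wrong comparator.* It can show whether classes draw disadvantaged women disproportionately. It is weak for judging how well the target group was reached, but it is not an error.

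**Conclusion.** The point holds in two parts. First, the only participant-level measure named for BIG-5 efficacy is a reach measure by the document's own usage, and it cannot show an effect on PA or health. This is stated positively in the text, so a longer protocol or an analysis plan would have to contradict the article to put it right. Second, the GET-10 PA questionnaire contradicts a table said to be complete and a data list that omits it. The claim of completeness makes this an inconsistency and not mere condensation.

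Severity is moderate. One of five RE-AIM dimensions is affected, and the main questions on recruitment, capacity and reach are untouched. The conclusion rests on the measures described in the article. If a full protocol schedules the GET-10 questionnaire before and after each course, the second part reduces to correcting Table 3 and the data list; the BIG-5 part would remain.

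**What to change.** 1. **Reach.** Move the BIG-5 demographic comparison to Reach. Add the target group's share of the community's inhabitants as a reference; the web and database search described under Recruiting Communities for Scale-Up already collects it. Remove the effectiveness tag from the attendance-list and waiting-list rows of Table 3. Cost: editing only.
2. **GET-10.** Add the PA questionnaire to Table 3 and to the list of quantitative data. Name the instrument, give it at the first and last session of each cycle, and report within-person change with everyone enrolled as the denominator, stating how many have no final value. Cost: two administrations in each of 40 cycles, 2 × 40 = 80 in all; the closing one can accompany the feedback form already handed out.
3. **BIG-5.** Choose one of two routes. Either add the same short PA items at the first session and on the existing feedback form, at the price of somewhat more form-filling in low-threshold classes. Or withdraw the BIG-5 efficacy claim and narrow the Conclusion so that it does not promise effects on that target group; this costs nothing in the field.

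Even with these changes the result is an uncontrolled before-and-after change, which the limitations section should say. Items 2 and 3 should be settled before the courses start.
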